## Abstract

**Background:**

Maintaining quality of care in family planning (FP) counselling in low-resource settings is challenging. Job aids can help providers give more accurate and client-specific advice but require a provider to use them effectively and consistently. Marie Stopes International (MSI) have designed the tablet-computer based Digital Counselling Application (DCA), which prompts structured, supportive, client-specific and unbiased FP counselling. We hypothesise that a systematic exploration of clients’ fertility intentions, medical eligibility and preferences will increase their uptake of long acting and permanent methods of contraception (LAPMs).

**Methods/design:**

We will conduct a two-armed, parallel, cluster randomised control trial across all MSI clinics (clusters) in Ethiopia (24) and Vietnam (11), randomising 18 clinics to the intervention group and 17 to the control group. Intervention providers will attend a two-day DCA-use training programme, and use DCA in their FP counselling sessions. Usual care providers will counsel clients as before. We aim to recruit 75 clients who have had FP counselling per clinic (2625 total), following them up via two telephone interviews, initially within 2 days and then at 4 months. The primary outcome is defined as the proportion of clients who report choosing a LAPM following FP counselling and will include switchers (FP counselling clients who switch from using any other FP method) and adopters (FP counselling clients who adopt any FP method having not previously been using one). We will also collect secondary outcomes at the initial follow-up (including the proportion of clients reporting being recommended a LAPM by a provider and a range of measures of client experience and satisfaction) and at the 4-month follow-up (including a range of measures of continuation rates for different FP method types). In the intervention arm, we will also conduct mixed-methods sampling to assess how providers use DCA (using an observational survey of provider–client interactions), and understand users’ experiences of receiving and giving DCA-based FP counselling (through in-depth interviews).

**Discussion:**

This trial will provide novel information on the feasibility and acceptability of health worker delivered FP counselling using DCA, with robust evidence on its effectiveness at increasing the uptake of LAPMs in low-resource settings.

**Trial registration:**

ISRCTN, ISRCTN11040557. Registered on 2 March 2017 (retrospectively registered).

**Electronic supplementary material:**

The online version of this article (10.1186/s13063-018-2815-0) contains supplementary material, which is available to authorized users.

## Background

Access to a choice of contraceptive methods is important throughout a woman’s reproductive life as her circumstances and preferences change over time [1]. A greater methods mix, or range of available family planning (FP) services, to address an unmet need is promoted by the World Health Organisation (WHO) [2, 3] and the United Nations [4].

FP service providers inform clients about available methods in different ways across the private and public sectors, ranging from group information sessions introducing all methods, to individual screening of a client’s needs and wants and supporting a client’s selection of methods. Paper-based handheld job aids, such as flipcharts, are often used as reference manuals by providers and decision-making aids for clients [5]. Information leaflets and posters, reproductive anatomy models and displays of contraceptive methods also support provider–client consultations, and the WHO eligibility wheel is also widely used in low-income countries to support providers in giving guidance on medically appropriate methods [6]. However, the application of these job aids varies across the private and public sectors, as well as between providers within the same organisation.

Maintaining quality of care in FP counselling services is vital for maximising service utilisation. Quality FP counselling requires that providers offer impartial advice on a broad mix of methods, by sharing details on side effects and effectiveness of methods [7, 8]. FP service providers must also understand their clients’ fertility intentions and address their concerns towards different methods [9]. Yet providers’ counselling can be confounded by various technical competency biases influenced by factors such as their training, cadre, time available to counsel sufficiently and demeanour [7, 10, 11]. Achieving quality FP counselling can improve client satisfaction, improve clients’ use of services, improve safe and effective use of contraceptive methods [5] and influence the likelihood of discontinuation or switching to another method [1].

Contraceptives are used by two-thirds of married or women in-union around the world, and almost 90% of contraceptive users use modern methods [4]. However, in 2015 less than half the total demand for FP to stop or limit childbearing was being met by modern methods, particularly in areas where contraceptive use is low, such as Africa, or where couples rely on traditional methods [4]. Contraceptive preferences and the promotion of methods varies by country [12]. In Africa, short-acting methods are more common whereas long-acting or permanent methods of contraception (LAPMs) are more common in Asia. These preferences are influenced by a country’s political history, access to a method mix and, in some cases, cultural preferences and provider bias [13]. In Ethiopia, the contraceptive prevalence rate is low (29%), and short-acting methods dominate the contraceptive method mix [14]. There is a skewed preference for injectable contraceptives (74%), despite community-level provision and a scaling up of long-acting methods since 2009 [14, 15]. However, use of implants is increasing, from 0.2 to 5% in 2014, and they are now the second most selected method [14]. In Vietnam, the contraceptive prevalence rate is much higher (65%), yet abortion rates are also high [16]. The two child per married couple policy of Vietnam in the 1960–1990s meant intrauterine devices (IUDs) and tubal ligation were the only modern methods promoted. However, for many women, IUDs are not medically appropriate [17] and this lack of contraceptive choice coupled with the social stigma of buying condoms and lack of knowledge of contraceptives has resulted in the highest abortion rate in Asia.

Marie Stopes International (MSI) seeks to help women choose a contraceptive method that suits their individual lifestyles and medical needs. In the past, MSI provided FP counselling training for providers that focused on the delivery of information from providers to the clients. More recently, MSI’s training has changed, placing greater emphasis on meeting the clients’ contraceptive needs and preferences. Currently, MSI providers use flipcharts to support their FP counselling sessions. However, providers typically use the flipcharts intermittently and there is substantial variation between providers’ consideration of clients’ circumstances and the suitability of methods recommend. This can result in providers offering unnecessary or an overwhelming number of options to clients, or just offering a subset of suitable options.

Therefore, given the increasingly affordable access to tablet computers, the Medical Development Team at MSI developed a tablet-computer based digital job aid, known as the Digital Counselling Application (DCA). The aim of DCA is to provide a tool that: (1) promotes interaction between providers and clients by forcing providers to ask clients a structured and systematic series of questions and (2) provides the client with a personalised list of recommended methods, based on an algorithm that uses information about the client’s situation, which the provider enters into DCA, removing the need for the provider to do this in their head (and thereby provide advice of varying quality of specificity). Women’s unmet need for modern methods, including LAPMs, is significantly associated with women’s education and empowerment, the quality of client counselling, partner discussions and exposure to media [18, 19].

In recognition of these factors, the intervention aims to support the uptake of modern methods through quality client-centred counselling. The intention is to standardise the quality of care in FP counselling to inform clients and empower them to select their preferred method. We hypothesise that DCA will offer a more client-focused counselling process, increasing providers’ consideration of clients’ circumstances and needs, reducing bias in provider recommendations, limiting discussion of all possible FP methods but expanding discussion on client-preferred methods (as ranked by DCA) designed to suit clients’ needs and preferences. This is anticipated to improve users’ counselling experience and increase clients’ readiness to consider and accept a LAPM. Our primary objective is, therefore, to evaluate the effects of DCA on LAPM uptake among clients attending FP counselling at MSI clinics in Ethiopia and Vietnam. We will also explore any effect of the DCA-led client-centred counselling on continuation rates of LAPM uptake, since providers are actively prompted to provide an upfront discussion of the side effects in advance of LAPM uptake compared to traditional counselling. The trial is also supported by a qualitative exploration of providers’ and clients’ experience of DCA, to identify where and how DCA can be improved.

## Methods/design

This protocol follows the Standard Protocol Items: Recommendations for Interventional Trials (SPIRIT) checklist (Additional file 1). The SPIRIT recommended schematic diagram detailing the schedule of enrolment, interventions and assessments is provided as Fig. 1.

**Fig. 1 Fig1:**
[figure not shown]
SPIRIT schedule. DCA Digital Counselling Application, FP family planning.

### Design and study setting

We will use a parallel-group, two-arm, cluster randomised controlled trial design to evaluate whether our intervention is superior to the existing treatment (control). We will conduct the study in MSI clinics (formally known as static service delivery centres) across Ethiopia and Vietnam. All clinics in Ethiopia and Vietnam are in urban areas, and typically serve clients with higher incomes than is average for the country. In 2015, 11% of Ethiopian clients and 1% of Vietnamese clients visiting clinics lived below the poverty line of $1.25. Although MSI charges clients for FP services, they have a policy of offering a discount or waiver for clients who cannot pay. Typically, the vast majority of clients self-refer after hearing of the services offered by MSI through social networks.

Clinics are staffed by formally trained clinicians (providers), who are employed and trained by MSI, and the intervention will be delivered by MSI FP providers at the clinic level, with the clinic being the unit of randomisation. A clustered design is necessary because it will not be feasible for clinic providers to switch between delivering the intervention (which involves training) or control treatment to clients. Moreover, this design avoids the risk of contamination between different providers within clinics. In addition to the trial, we will use a structured observational survey to explore how providers are using DCA and counselling clients in the intervention arm. We will also conduct a qualitative study using in-depth interviews with providers and clients to understand their experiences of using and receiving DCA-led FP counselling, respectively, which will also help us understand if and how it can be improved.

### Participants, recruitment and consent

We will invite all MSI clinics in Ethiopia (24) and Vietnam (11) to participate in the study, via the respective MSI in-country directors. All providers will be invited to participate, and we will seek verbal informed consent from providers for their participation, but only those passing an assessment of their knowledge of the intervention at the end of the intervention training will be eligible to continue to participate.

Eligible participants will be women aged 18–49 years old who present at MSI clinics and receive FP counselling. During the recruitment phase of the trial, we will recruit participants across all participating clinics as they present consecutively for FP counselling, until clinics reach their target sample size. Clients attending MSI clinics for FP counselling will initially be asked, either by the receptionist or by the provider (if there is no receptionist), if they can be contacted by a researcher via telephone in the next 2 days who will ask them some questions about their experience of the study. Those who agree will then be telephoned in the next 2 days by a researcher for an exit interview. The researcher will then seek formal verbal informed consent from the client to conduct the exit interview and provide outcome data for the trial. They will also be asked if they can be contacted again at 4 months for a follow-up interview. Those clients who agree will then be contacted at 4 months after their FP counselling session by a researcher, again via telephone. Again they will first seek formal verbal informed consent for the interview before collecting the 4-month follow-up data. At both the initial and 4-month telephone interviews, clients who agree to be contacted but who do not answer their phone or are otherwise busy will be contacted again twice more over subsequent days, before being recorded as lost to follow-up. For clients lost to follow-up, their anonymous basic demographic data along with their choice of FP method will be collected from their clinic’s routine records (see Section 2.13 on statistical analyses for details of which patients will be included in the analyses). Clients will not receive remuneration for their time.

We will also conduct a structured observation survey of provider–client interactions during FP counselling sessions in intervention arm clinics. For this survey, providers will be asked to participate by a researcher, who will seek their written informed consent. The survey will then be carried out in each participating clinic over the course of a day or two, with all clients attending the clinics for FP counselling being asked to participate in the survey by the researcher, who will again seek their written informed consent. An overview of the different quantitative and qualitative components in the trial and their interlinkages is provided in Fig. 2.

**Fig. 2 Fig2:**
[figure not shown]
Study components flow diagram. DCA Digital Counselling Application, FP family planning, MSI Marie Stopes International

### Intervention

MSI developed the intervention as part of their initiative to promote client-centred counselling on FP (particularly the provision of contraception) across all 31 countries where they operate. The intervention consists of two components: DCA and an integrated training package.

DCA is a software application that runs on an electronic tablet and, led by the provider, guides the client through a series of questions, supported by visual aids. The device and training package were developed by the Medical Development team at MSI and pilot tested in MSI clinics in South Africa to encourage feedback on its usability and content. DCA is intended for day-to-day use by trained providers during FP counselling sessions. By prompting a structured and systematic discussion and exchange of relevant information between providers and clients about the client’s preferences, it is hoped DCA will lead to more supportive, interactive and unbiased counselling sessions.

DCA prompts the user (the provider) to ask each client a series of key questions, starting with whether they are currently using a FP method. If yes, they are asked whether they are satisfied, and if no whether they have a FP method in mind or are open to exploring other methods. The clients’ answers to these questions then send them down one of three pathways. Pathway 1 is called the satisfied user check-in, and is intended for clients seeking to renew their FP method. Pathway 2 helps the client to explore all methods, and is intended to be used by contraceptive users who are not satisfied with their current method or by clients who are not currently using any method. Pathway 3 is designed to support clients with a method in mind but who are not currently using contraception.

The application gathers basic information on the client, their medical eligibility and their lifestyle, and at the end of the process provides a list of recommended methods based on the information provided, with those best fitting the clients’ responses listed at the top. The provider is then encouraged to discuss the pros and cons of the top three ranked methods with the client to explore the clients’ preferences and to help them make a decision about which contraceptive method best fits their lifestyle and needs. DCA has been designed to base its ranking of methods on clients’ fertility intentions and how effective (with regard to failure rates) the method is. The application also reflects the methods available at each centre. The application is not designed to explicitly promote the uptake of LAPM, but DCA’s intention is to offer client-centred counselling responsive to clients’ needs, which we expect to lead to an increased uptake of LAPM as more suitable and effective methods for many women’s FP needs. This means DCA is designed to prompt the provider to identify each client’s fertility intentions, medical eligibility and individual preferences, and inform each client of the possible side effects and complications of methods deemed by DCA most suitable to them. Side effects and complications are commonly left undiscussed, and so we also seek to explore if client-centred counselling and an upfront discussion of the barriers to uptake have any effect on clients’ continuation rates. Providers using DCA will discuss the most suitable methods with the client (including misconceptions, side effects and benefits) and thereby increase clients’ readiness and likelihood of accepting a suitable LAPM option (which offers greater effectiveness).

The integrated training package will consist of a 2-day programme delivered to FP providers in Ethiopia and Vietnam by MSI UK and in-country programme staff. The first day of the programme will consist of a 45-min presentation and group discussion on client-centred counselling (what it is, barriers to achieving it, how it may be different to usual counselling and its potential benefits), a 90-min introduction to DCA (including using the tablet and the application), a 90-min detailed review of the DCA content (exploring hypothetical client journeys through the application) followed by a 75-min session for hands-on practice with the application and reflection. Day two of the programme will consist of a further practice session with the application using two role plays, followed by knowledge tests and practical assessments. We will deliver the training package to all clinic providers in the intervention arm as a group workshop in Vietnam and then Ethiopia. The same training format and role plays will be used to promote consistency in providers’ interpretation of the scenarios and use of the application during those scenarios. The output of the training will involve a true/false knowledge test on contraceptive methods, and providers will be included in the trial only if they pass all questions.

Following implementation of the intervention, UK-based MSI project staff will remain in close contact with in-country MSI project staff to promote adherence to the intervention by providers in the intervention arm and to monitor the conduct of the trial.

### Control

In the control arm, clinics providers will continue to offer the usual provider–client FP counselling service. Typically, this means providers offer an overview of most or all methods before asking the client to select one. However, if providers in control arm clinics have not received MSI’s existing standard training on client-centred counselling within the last 18 months then they will receive refresher FP training. Providers in both the control and intervention arms will have access to their existing job aids, such as posters, diagrams, flipcharts, anatomy models and the WHO contraceptive wheel. Only providers in the intervention arm clinics will have access to and be given training on DCA and the tablets used to run DCA.

### Existing procedures

Aside from the intervention procedures, and the recruitment, consent and data collection processes, clinics in both arms will be allowed to operate as normal with no other changes to their day-to-day practices.

### Primary outcome

The primary outcome will be reported LAPM uptake. This is defined as the proportion of switchers and adopters who report choosing a LAPM following FP counselling (rather than a short-acting method). Switchers are clients using any FP method at the time of counselling who then change to any other FP method following counselling. Adopters are clients who are not using any FP method at the time of counselling but who decide to start using any FP method following counselling. LAPM methods include contraceptive implants, IUDs, intrauterine systems and tubal ligation, with all other FP methods considered short-acting methods. This outcome will be calculated from data collected at the initial telephone exit interview, and its accuracy is, therefore, dependent on the accuracy of clients’ responses. This primary outcome (reported LAPM uptake) is already used by MSI as a clinic performance indicator, making it feasible to collect this information. It is also a key indicator of FP practices supporting sustainable development goals 3 and 5.

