### Statistical analyses

We will use methods suitable for cluster trials with relatively few clusters, analysing cluster-level summary measures (proportions) of all binary outcomes to account for between-cluster variation, and reporting crude and covariate-adjusted results [21]. We first will convert all Likert and numeric scale outcomes into binary scale outcomes. As laid out above, the four-point Likert scale outcomes will be dichotomised by combining the first two categories and then the final two categories. The two 5-point Likert scale outcomes will be dichotomised by combining the first two categories and then the final three categories. The five-point numeric scale outcomes will be dichotomised by combining the first three categories and then the final two categories. For all outcomes, we will first estimate the crude intervention effect as the difference between the mean intervention arm and mean control arm cluster-level outcome proportions (i.e. a risk difference), and we will estimate the 95% confidence intervals and *p* value associated with this effect size estimate using an independent *t*-test.

We will then estimate covariate-adjusted results using a two-stage method [21]. First, using a logistic regression model, we will model the effects of our covariates of interest on the individual-level binary outcomes, while excluding the effect of treatment. We will then use the individual-level model predicted values and the individual-level observed values for each outcome to calculate covariate-adjusted cluster-level difference residuals. Lastly, we will use these values in place of cluster-level summary outcome measures to estimate covariate-adjusted risk differences, and again use *t*-tests to estimate the associated 95% confidence intervals and *p* values. We will adjust outcomes for covariates as shown in Table 1. In addition, using the methods outlined in Hayes & Moulton [21] for analysing cluster-level effect modification, we will assess whether the treatment effect differs for the primary outcome between the following subgroups: Ethiopia vs Vietnam and switchers vs adopters.

**Table 1 Tab1:** Planned covariate adjustment for covariate-adjusted analyses

Outcome	Covariates adjusted for
Primary (LAPM uptake among FP switchers and adopters)	1–8
Proportion of clients recommended a LAPM by their provider	1–8
How well clients felt providers listened to their needs	1–8

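### The primary denominator (switchers plus adopters) is formed after counselling, so the LAPM proportion can move in either direction with no change in LAPM choosers per counselled client

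*Protocol article*

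**What the plan says.** The Primary outcome section sets the measure as the "proportion of switchers and adopters who report choosing a LAPM following FP counselling (rather than a short-acting method". It then defines the two groups that form the denominator.

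- For women already using a method: "Switchers are clients using any FP method at the time of counselling who then change to any other FP method following counselling". A woman who stays with her method is therefore not counted.
- For women using none, the rule is parallel: "Adopters are clients who are not using any FP method at the time of counselling but who decide to start using any FP method" after the session. A woman who leaves without a method is likewise not counted.

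Recruitment is wider. Under Participants, recruitment and consent, "Eligible participants will be women aged 18–49 years old who present at MSI clinics and receive FP counselling". The last paragraph of the Background puts the primary objective in the same wide terms: the effect of DCA on LAPM uptake in clients who attend FP counselling at the clinics.

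The Sample size section applies its 40% control rate to switchers and adopters, and Table 1 labels the primary outcome the same way. One of the two planned effect-modification analyses of the primary outcome also uses these groups: "Ethiopia vs Vietnam and switchers vs adopters".

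**The concern.** Randomisation makes the clients attending intervention and control clinics comparable on average. It does not do so for a subset chosen by behaviour that follows exposure to the intervention. A current user counts only if she changes method, and a non-user only if she starts one. Counselling may influence either decision.

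The Intervention section gives DCA a route for users who want to renew and another in which dissatisfied users and non-users explore all methods. An effect on who switches, renews, adopts or leaves with nothing is therefore plausible. If there is one, the ratio mixes two things: how many women choose a LAPM, and how many make any change at all. A difference could then appear with no additional LAPM user, or a real gain could be hidden. The same weakness affects the switcher/adopter subgroup comparison.

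**Working it through.** **Inputs.** From Sample size: control rate 40%, target 50.5%, 18 and 17 clinics, 75 clients per clinic, between-cluster coefficient of variation 0.2, 5% level. From Statistical analyses: two-sided test, and 10.5 points as the clinically significant increase. The share of counselled clients who become switchers or adopters is not given; I take 60% to 100% as an assumption.

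**The plan's own figure.** Variance per cluster = p(1-p)/m + k²p², with m = 75 and k = 0.2.

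- Control: 0.24/75 + 0.04 × 0.16 = 0.0096.
- Intervention: 0.249975/75 + 0.04 × 0.255025 = 0.01353.
- With the usual allowance of one cluster per arm (17 and 16 effective): SE = √(0.01353/17 + 0.0096/16) = 0.0374.
- z = 0.105/0.0374 - 1.96 = 0.85, so power is 80.2%.

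A non-central t calculation with 33 degrees of freedom also gives 80.2%. The stated 80% reproduces.

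**Effect of the denominator alone.** Hold the number of LAPM choosers fixed and let the switcher-plus-adopter group change by a fraction f. The primary proportion becomes 0.40/(1 + f), whatever the starting share.

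| Change in denominator | Primary proportion | Shift (points) |
|---|---|---|
| -20% | 50.0% | +10.0 |
| -10% | 44.4% | +4.4 |
| -5% | 42.1% | +2.1 |
| +5% | 38.1% | -1.9 |
| +10% | 36.4% | -3.6 |
| +20% | 33.3% | -6.7 |

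The shrinkage that gives the full target effect is 1 - 0.40/0.505 = 20.8%. In every row the difference in LAPM choosers per counselled client is zero.

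**How large these changes are.** Short-acting choosers make up 60% of the control denominator. Shrinkage of 5%, 10% or 20% therefore means losing 8.3%, 16.7% or 33.3% of them (0.05/0.60, 0.10/0.60, 0.20/0.60). Growth of 20% is possible only if at most 1/1.20 = 83% of control clients switch or adopt.

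**Worked case, assumed share 80%.** Of 75 clients, 60 switch or adopt and 24 choose a LAPM: 24/60 = 40%, and 24/75 = 32% of all clients. If 12 fewer women take up or switch to a short-acting method, the result is 24/48 = 50%, still 32% of all clients. The reverse also occurs. If LAPM and short-acting choosers both rise by 10%, the primary proportion stays at 26.4/66 = 40%, while uptake per counselled client rises from 32% to 26.4/75 = 35.2%.

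**Does anything in the plan repair this?**

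- Analysis by original clinic allocation keeps clinics in their arm but does not bring back the excluded clients.
- Covariate adjustment works within the selected group.
- No listed outcome measures LAPM uptake among all counselled clients. The nearest secondary outcome concerns LAPM recommendation by the provider.

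**Side effect on power.** The calculation treats all 75 clients per clinic as evaluable. At shares of 90%, 80%, 70% and 60%, power for the same effect is 79.0%, 77.5%, 75.6% and 73.1%.

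**The case against.** The best defence is that the choice of a LAPM over a short-acting method, among women who change or start, is a coherent method-mix question, and the clinics already use it as an indicator. That stands as a reason to keep the measure. It supports feasibility and continuity, but it does not make the measure a valid contrast between arms. It is also fair that recruitment began in January 2017, so replacing the primary outcome now would have a credibility cost of its own.

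Four stronger readings are tempting, and the article does not support them.

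- **That DCA pushes satisfied users to renew.** The text says "Pathway 1 is called the satisfied user check-in, and is intended for clients seeking to renew their FP method"; clients reach it through their own answers. An effect on who enters the denominator is possible but not documented.
- **That the abstract contradicts the Primary outcome section.** The abstract opens with "The primary outcome is defined as the proportion of clients who report choosing a LAPM following FP counselling", but the same sentence goes on to say that switchers and adopters are included and defines both. It is looser wording, not clearly a different denominator.
- **That the trial will show a false benefit.** The distortion can run either way. The largest shifts need large changes in behaviour, and a 5% to 10% shrinkage gives only +2.1 to +4.4 points.
- **That a denominator fixed on arrival fully restores randomisation.** Clients still enter only by agreeing to be telephoned, in clinics where providers know their allocation.

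Restricting the analysis to women not using a LAPM on arrival would also have a drawback. The current outcome counts LAPM users who switch, so moves away from a LAPM would drop out of sight.

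**Conclusion.** The concern holds as a statement of what can happen. The denominator is settled after randomisation and after exposure to DCA, it is narrower than the stated objective, and no listed analysis shows whether the arms differ in who enters it. Over the assumed range of a 20% smaller to a 20% larger denominator, the shift runs from +10.0 to -6.7 points, against a threshold of 10.5. These figures assume 40% in control and an unchanged number of LAPM choosers. The actual size and direction cannot be known from the article. The stated sample size is not itself wrong. The point supports adding a pre-specified analysis that guards the main conclusion; it does not require the existing indicator to be abandoned.

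**What to change.** Before analysis:

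1. Pre-specify LAPM uptake with a denominator fixed before counselling: all counselled clients who give an exit interview, with no method or an unchanged short-acting method counted as no LAPM uptake. State a rule for women already using a LAPM on arrival, and add a sensitivity analysis that excludes them.
2. Require this analysis to agree before claiming that DCA raises LAPM uptake, and say in advance what agreement means.
3. Report by arm the share of clients who switch, adopt, renew or leave with no method.
4. Define the subgroup as method users versus non-users on arrival, in place of switchers versus adopters.
5. Keep the switcher/adopter proportion as the clinic indicator.

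No new contact with clients should be needed, because identifying switchers and adopters at the exit interview already requires the method before and after counselling. Arrival status should come from that information and not from covariate 6 in Table 1, which merges short-acting users with women unsure of their method.

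The cost is a little more analysis and a restated power statement. The 40% and 80% figures apply only to switchers and adopters. At assumed shares of 80% and 60%, control uptake among all clients would be 0.80 × 40% = 32% and 0.60 × 40% = 24%, before applying the rule for women arriving on a LAPM.
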